### Blinding and randomization

Participation occurs sequentially. At the time that a subject has an established date of operation, the physician checks the criteria are being met. If so, the potential participant is informed of the study and is referred to the rehabilitation department where, if is definitely admitted will take part in the randomization process. The randomization is generated from the output of the Matlab® statistical program by external assessor. A physiotherapist with 3 years of experience and blinded to the intervention groups will be in charge of the outcome assessment. The blinding of the participants is not assured, as they are informed about the trial before randomization. Neither is it the blinding of those who provide the treatments for the same reason. However, physiotherapists do not take part in the process of randomization and participant allocation. The external assessor in charge of the randomization is blinded to the intervention groups that have a numerical coding, and will receive the data of the participants for the statistical processing. The interpretation of the results will be carried out by the whole team.

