#### Outcome assessment

The baseline assessments will be carried out by a physiotherapist blinded to the interventions, following the signing of an informed consent form and prior to the start of the physiotherapy sessions. The proposed time for the outcome evaluation is in the preoperative period (baseline, between 8 and 4 weeks), before (1 week) and after (2 weeks) the surgical procedure, after the postoperative intervention (6 weeks) and 12 months follow-ups. Details are given in Table 2.

**Table 2 Tab2:** Detail of variables and times for evaluation of outcomes

Time point	Enrolment	BL	BP	AP	AI	12 m
Eligibility screen	x					
Informed consent	x					
Randomization	x					
Assessments						
Demographic and biomedical	x					
Primary						
Self-reported functionality	KOOS	x	x	x	x	x
Balance (overall)	Berg Balance Scale	x	x	x	x	x
Secondary						
Function	ROM (flexion)	x	x	x	x	x
	ROM (extension)	x	x	x	x	x
	Strength	x	x	x	x	x
Balance (dynamic)	Timed Up & Go	x	x	x	x	x
(static)	One-leg Stand	x	x		x	x
(stability)	Functional Reach	x	x	x	x	x
Quality of Life	EuroQoL	x			x	x
Anxiety	EuroQoL(5D)	x	x		x	
Cost-effectiveness						
	Qaly					x
Patient expectations						
		x			x	x
Interventions		BL	BP	AP	AI	12 m
Non-active comparator				x------x		
In-hospital preoperative		x------x		x------x		
In-home preoperative		x------x		x------x		

*BL* Baseline, *BP* Before procedure, *AP* After procedure, *AI* After intervention, *KOOS* Knee Injury Osteoartritis Outcome Score, *ROM* Range of Movement in degrees, *Qaly* Quality adjusted life year

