### Data analysis

The implementation of protocols will be presented with descriptive statistics. In an exploratory way, the drop-out ratios will be estimated and the survival analyses will be used [29]. This aspect will also be taken into account throughout the follow-up and registering when drop-outs occur. The incidence of adverse effects at 6 weeks will be evaluated, which will be categorized according to whether they are considered to be definitive, probable or possibly related to the interventions.

It is hypothesized that the experimental groups will have enhanced balance abilities, which may also have a direct impact on functionality in the short and mid-term. All temporal instants are of interest, although particular attention will be paid to the early postoperative effects (6w) and maintenance of potential mid-term benefits (1y).

The data analysis will include the sample descriptors, a comparison of the baseline condition with the t tests that will be parametric or not depending on the results of the tests of Wilcoxon and Shapiro-Wilk, and a comparison of the progress due to the results of the intervention with an ANOVA analysis of repeated measures, looking for interactions initially as a function of time, group, and time per group. In case of baseline differences between the participants, an ANCOVA analysis will be conducted instead, in which the data will be adjusted to the baseline scores. Analyses will be performed for primary and secondary outcomes. Post-hoc analyses will be performed accordingly. The significance levels will be set at 95%.

A qualitative analysis will be carried out in which it will be estimated if the obtained progressions measured as the mean values of the difference between the basal and final values for each variable at each time point reach the minimum established according to the psychometric properties referring to the minimum clinical importance difference or minimum detectable change with a CI of 95%, if they are available in the literature. If they had been reported by different studies, it would be based on the suggested minimum value.

A post-hoc power analysis and an estimate of the effect size will be implemented with the tool G*Power [20], based on Cohen’s *d* and considering a low, medium or high effect as a function of the result [30].

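### A baseline comparison chooses the model for every outcome: fix one baseline-adjusted model in advance

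*Protocol article*

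**What the plan says.** All of this is in the protocol article, mostly under Data analysis.

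- Progress is compared "with an ANOVA analysis of repeated measures, looking for interactions initially as a function of time, group, and time per group". Table 2 schedules KOOS and the Berg Balance Scale at five times, the first being baseline, so baseline is one of the outcome times in this model.
- Before that comes "a comparison of the baseline condition with the t tests that will be parametric or not depending on the results". Two distributional checks are named for that choice, Wilcoxon and Shapiro-Wilk.
- The switch is: "In case of baseline differences between the participants, an ANCOVA analysis will be conducted instead". The ANCOVA takes each participant's baseline score into account.
- The scope is wide: "Analyses will be performed for primary and secondary outcomes".

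A general 95% level closes the paragraph. It is not tied to the switch, and nothing says which variables or which pairs of arms count as showing baseline differences.

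The Sample size section sizes the trial on the Berg scale by one-way ANOVA without a baseline covariate: 53 against 48 points, SD 4.5, alpha 0.05, 20 per group, 75 in total after loss.

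**The concern.** Design and ethics describes a three-arm randomised trial. If allocation worked, any difference between arms at baseline arose by chance, and a significance test of it answers no useful question. Here the test does more than describe the sample, because it decides which model estimates the treatment effect. With no stated trigger, that decision can be settled after the data are seen, and KOOS and Berg could end up under different models.

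The tools named also fit poorly. A t test compares two groups and there are three, so several tests per variable would be needed. Wilcoxon is a comparison of location and cannot show whether a parametric test is suitable.

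What is at stake is precision. Baseline scores are collected on everyone for both primary outcomes, and their value as a covariate does not depend on an observed imbalance. The default gives that value up in most trials.

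**Working it through.** **Inputs from the Sample size section.** Means 53, 53 and 48; SD 4.5; alpha 0.05; 20 per group; 20% loss; a stated floor of d > 0.8. The planned effect is d = 5/4.5 = 1.11.

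**Inputs assumed.** The documents give no baseline-to-follow-up correlation ρ, so 0.3, 0.5 and 0.7 are shown. No trigger is defined, so it is taken as any of the three pairwise baseline t tests with p < 0.05, two-sided.

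**Step 1: the plan's own figure.** The grand mean is 51.33 and the deviations are 1.67, 1.67 and −3.33. Their root mean square is 2.357, so f = 2.357/4.5 = 0.524. With 60 participants the noncentrality is 60 × 0.524² ≈ 16.5, and one-way ANOVA has 95.2% power. No target power is stated, but 20 per group is the smallest size reaching 95%. Then 60/0.80 = 75. Both stated sizes reproduce.

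**Step 2: why adjustment gains.** At one follow-up visit, with equal SD σ at both times:

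- change from baseline has variance 2(1 − ρ)σ²;
- ANCOVA has residual variance (1 − ρ²)σ²;
- the ratio is 2/(1 + ρ), which is 1.54, 1.33 and 1.18 at ρ = 0.3, 0.5 and 0.7.

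The change score stands in for the group-by-time contrast, because repeated-measures ANOVA already contains baseline as a time.

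**Step 3: the two-stage rule.** Simulation with 40,000 trials per cell, three arms of 20, both experimental arms d above control, and the three-group F test. ANCOVA is used if the trigger fires; otherwise change score is used. Figures are % power.

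| d | ρ | Change score always | Two-stage rule | ANCOVA always | Loss (points) |
|---|---|---|---|---|---|
| 1.11 | 0.3 | 85.9 | 87.6 | 96.6 | 9.0 |
| 1.11 | 0.5 | 95.3 | 96.0 | 98.6 | 2.6 |
| 1.11 | 0.7 | 99.7 | 99.8 | 99.9 | 0.1 |
| 0.8 | 0.3 | 57.1 | 58.5 | 75.7 | 17.2 |
| 0.8 | 0.5 | 72.2 | 73.5 | 83.7 | 10.2 |
| 0.8 | 0.7 | 91.8 | 92.4 | 95.1 | 2.7 |

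Repeat simulations of the same set-up put the loss at d = 1.11 and ρ = 0.3 at 8 to 9 points.

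**Step 4: trigger rate and type I error.** The trigger fires in about 12% of trials per outcome by chance alone, so about 88% stay with the less precise analysis. With no treatment effect, the two-stage rule rejects in 3.8, 4.0 and 4.5% of trials at ρ = 0.3, 0.5 and 0.7, slightly below nominal.

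**The case against.** Several points on the other side stand.

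- **Power at the planned effect is already high.** With ρ of 0.5 or more, the rule has at least 96% power at d = 1.11, and the loss is under 3 points. However, 1.11 is an assumption about Berg only. No effect is given for the co-primary KOOS function scale.
- **The simulation is simpler than the plan.** It uses one visit and a change score in place of the time-by-group test over five visits. The effect on that test is not shown, and the trigger is assumed.
- **A later analysis plan may add detail.** The conditional rule, though, is stated outright. A later document would have to reverse it, not complete it.

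A reader might also infer four stronger things that the documents do not support.

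- **That the trial forfeits 3 to 18 points of power as a fact.** That range needs an unstated correlation and uses the protocol's floor of d = 0.8, not its planned effect.
- **That choosing the model from the data inflates false positives.** The simulation shows the reverse.
- **That everyone missing one of five visits is lost.** Dealing with missing data plans home completion of surveys, evaluator visits, and imputation with an intention-to-treat reanalysis, and the 75 already allows for loss.
- **That baseline KOOS is biased by knowledge of the arm.** Table 2 lists randomisation under Enrolment, ahead of the baseline column, and Outcome assessment places baseline "following the signing of an informed consent form and prior to the start of the physiotherapy sessions". Yet Blinding and randomization says only: "The blinding of the participants is not assured, as they are informed about the trial before randomization". That is knowledge of the trial, not of the arm. No text says the arm is known before baseline KOOS is answered, so this calls for clarification only.

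**Conclusion.** The concern holds as a matter of precision and pre-specification, and should be fixed. The stated rule lets chance imbalance select the model for both primary and all secondary outcomes, with an undefined trigger and tests unsuited to three arms.

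The cost in power is from about 8 or 9 points down to under 1 at the planned d = 1.11, and from about 17 down to 3 at d = 0.8, as ρ goes from 0.3 to 0.7. These figures rest on the assumed correlation, a single follow-up visit, the change score as stand-in, the assumed pairwise trigger and 20 evaluable per arm. The direction of the variance comparison does not depend on the exact correlation: 2/(1 + ρ) exceeds 1 for every ρ below 1. Validity in the sense of type I error is not threatened.

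**What to change.** Delete the baseline significance tests and the conditional sentence, and describe baseline by arm without p values. Put one rule in their place, for example: every outcome will be analysed by a linear mixed model on its scheduled post-baseline visits, with arm, visit, arm-by-visit and baseline score as fixed effects, whatever the baseline comparison shows; arm contrasts will be read at 6 weeks and 1 year. Those are the two times that Data analysis already singles out. An outcome that Table 2 does not schedule at 12 months, such as the anxiety item, is read at 6 weeks only.

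As a separate clarification, state whether baseline KOOS is completed before participants learn their arm. Recruitment began in March 2017, so this should record what is actually done. Editing Table 2 cannot change the order for those already enrolled.

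The cost is the rewording of one paragraph and one clarifying sentence, reported as a protocol change with its reason, as the Discussion promises for substantial changes. No new data, visits or participants are needed.

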#### Dealing with missing data

Every effort will be made to reduce sample loss, particularly with regard to mid-term monitoring (1y). In the event that a participant cannot or decides not to attend the follow-up evaluation, it is proposed to resolve the self-reported surveys at home and forward them via email, or the possibility of the evaluator’s displacement is also granted. To deal with missing data, we will compare the baseline characteristics of those patients who have and have not been evaluated in search of potential sources bias in the results of the complete analyses. It is also intended to obtain a record of the reasons for drop-out and then evaluate the best mechanism of data analysis, with methods to impute data and reanalyze it with the intention to treat, and thus evaluate the possible impact on the conclusions [31].

#### Economic evaluation

An economic analysis will be carried out to evaluate the cost-effectiveness of the experimental proposals versus the non-active comparator proposal. This will take into consideration all costs that are potentially related to each intervention, to the resources related to the training of the participant in the hospital, or in the case of performing the intervention at home, related to education and the time invested in monitoring the participant in order to ensure the compliance with the treatment. Appropriate unit costs will be allocated according to data from the national health system, including not only the time spent by physiotherapists but also by physicians [32].

The measure of effectiveness will be based on the results of the EuroQoL-5D, which will be used to estimate Quality Adjusted Life Years (QALY) estimated with the Spanish intervention rate associated with the time trade-off method. The analysis will be based on the mean overall cost and mean overall effect of each intervention. If a technique is less costly and more effective it will be deduced that it is cost-effective and therefore the one that will best optimize the use of resources. The acceptability curve will be plotted for the estimation of uncertainties. Finally a sensitivity analysis will allow to know the robustness.

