**Methods:**

Seventy-five participants will take part. The trial will include in-home and supervised hospital experimental training compared to a non-active control group in order to estimate the actual effect of the proposal against the benefits due exclusively to the surgical procedure. Interventions last 4 weeks prior to surgery, and the follow-up will be at 2w, 6w, and 1y following the operation. The primary outcomes are in agreement with the goals: self-reported functionality in terms of KOOS and overall balance in terms of the Berg Balance Scale. The secondary outcomes will include the measurements of static and dynamic balance abilities, pain, function, and quality of life.

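### The cost-effectiveness comparison rests on mean effect per arm and names no adjustment for baseline EQ-5D, which gives up precision in the incremental QALY with about 20 evaluable patients per arm

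*Protocol article*

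**What the plan says.** Under Economic evaluation, the protocol article names the effect measure: "The measure of effectiveness will be based on the results of the EuroQoL-5D, which will be used to estimate Quality Adjusted Life Years (QALY". It then names the comparison: "The analysis will be based on the mean overall cost and mean overall effect of each intervention". No covariate or regression follows. The section adds an acceptability curve and a sensitivity analysis whose content is not given.

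Table 2 (Outcome assessment) schedules the EQ-5D three times: "Quality of Life EuroQoL x x x". The crosses fall at baseline, after the postoperative intervention (6 weeks) and at 12 months. On the timing of baseline the text says "The proposed time for the outcome evaluation is in the preoperative period (baseline, between 8 and 4 weeks".

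Baseline adjustment appears under Data analysis: "In case of baseline differences between the participants, an ANCOVA analysis will be conducted instead, in which the data will be adjusted to the baseline". The scope follows: "Analyses will be performed for primary and secondary outcomes". The outcome list places the EuroQoL-5D among the secondary outcomes and cost-effectiveness in a third group, Other outcomes. A regression with covariates is named elsewhere only for the planned pooling with a second trial.

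**The concern.** Baseline utility affects a QALY difference in two ways. It is the first point of the area under the utility curve, and it is usually correlated with the later points. A chance baseline difference between arms therefore carries into the incremental QALY, and variation that baseline could explain stays in its standard error.

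The plan's own baseline rule does not clearly help. Read literally, it covers the EQ-5D score as a secondary outcome but not the QALY or the cost-effectiveness result. If it were extended to QALYs, it would act only once a baseline difference had been found, and with groups this small a test misses sizeable imbalances.

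At stake is the precision of the figure behind the economic conclusion. The article gives that conclusion as one of the trial's purposes.

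**Working it through.** **Inputs from the protocol.** 20 evaluable per group and 75 in total (Sample size); EQ-5D at baseline, 6 weeks and 12 months; baseline 4 to 8 weeks before surgery; "the follow-up will be at 2w, 6w, and 1y following the operation".

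**Assumptions, not in the documents.** QALY by the trapezoid rule; EQ-5D SD 0.15 to 0.30, equal at all visits; baseline/follow-up correlation ρ of 0 to 0.5; correlation 0.6 between the two follow-ups.

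**1. The plan's own figure.** Means 53, 53 and 48 with SD 4.5 give f = √[(1.667² + 1.667² + 3.333²)/3]/4.5 = 0.524. With 20 per group the ANOVA has 95.2% power, and 60/(1 − 0.20) = 75. So 20 evaluable per arm is the right number to carry forward (25 randomised).

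**2. QALY weights.** On baseline, 6 weeks and 12 months:
- baseline 4 weeks before surgery: (5, 28, 23)/52
- baseline 8 weeks before surgery: (7, 30, 23)/52

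**3. Gain from adjustment.** Let V = SD²·w′Rw, with R the correlation matrix. Unadjusted SE = √(2V/20). The slope of QALY on baseline is b = w₀ + ρ(w₁ + w₂). The share of variance removed is b²/(w′Rw).

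Example with SD 0.20, ρ = 0.5, 4 weeks:
- w′Rw = [25 + 784 + 529 + 2(0.5·5·28 + 0.5·5·23 + 0.6·28·23)]/2704 = 2365.8/2704 = 0.875
- V = 0.04 × 0.875 = 0.0350, so SE = √(2 × 0.0350/20) = 0.0592
- b = (5 + 0.5 × 51)/52 = 0.587, so the share removed is 0.344/0.875 = 39.3%
- adjusted SE = 0.0592 × √0.607 = 0.0461

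| ρ | Baseline | Variance removed | SE at SD 0.20, unadjusted → adjusted |
|---|---|---|---|
| 0 | 4 wk | 1.2% | 0.0559 → 0.0555 |
| 0 | 8 wk | 2.1% | 0.0584 → 0.0578 |
| 0.3 | 4 wk | 18.2% | 0.0579 → 0.0523 |
| 0.3 | 8 wk | 20.7% | 0.0612 → 0.0544 |
| 0.5 | 4 wk | 39.3% | 0.0592 → 0.0461 |
| 0.5 | 8 wk | 41.9% | 0.0629 → 0.0480 |

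The percentages do not depend on the SD.

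**4. Cost of estimating the slope.** For two arms of 20 the adjusted variance is multiplied by about 1 + 1/(2·20 − 4) = 37/36. The 18.2% becomes 1 − 0.818 × 37/36 = 16%, and the 41.9% becomes 1 − 0.581 × 37/36 = 40%. At ρ = 0 the small gain turns into a loss of about 1 to 2%.

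**5. Higher correlation.** With baseline at 6 weeks, weights (6, 29, 23)/52 and ρ = 0.7 between all visits:
- w′Rw = [0.3 × 1406 + 0.7 × 58²]/2704 = 1.027
- b = (6 + 0.7 × 52)/52 = 0.815
- share removed = 0.665/1.027 = 64.7%, or about 64% after the factor in step 4

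**6. Exposure to imbalance.** The SE of the baseline difference is SD × √(2/20), which is 0.047 to 0.095 utility for SD 0.15 to 0.30. At SD 0.20 it is 0.063, and a 5% test flags only differences beyond about 1.96 × 0.063 = 0.124. An imbalance just short of that would escape the conditional rule. Multiplied by b, it would move the QALY difference by 0.048 (ρ = 0.3, 4 weeks) to 0.080 (ρ = 0.5, 8 weeks). At ρ = 0 the shift is 0.012 to 0.017.

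**The case against.** The strongest objection is that the plan is silent on adjustment, not wrong. Mean cost and mean effect per arm are the ordinary inputs to an incremental cost-effectiveness ratio, and the wording is compatible with regression-adjusted means. A condensed article may leave covariates to an analysis plan, and an unspecified sensitivity analysis is promised. This stands against anyone who infers that the article prescribes raw, unadjusted means: it does not use such a word. It does not remove the point, because the article does fix the basis of the comparison, states a baseline rule for other outcomes and does not extend that rule to QALYs.

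Second, randomisation leaves the unadjusted difference unbiased, and its standard error and the acceptability curve already carry the noise from chance imbalance. This stands. The loss is precision, plus error conditional on whatever imbalance occurs; none has been observed.

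Third, adjustment does not make the economic result decisive. An adjusted SE of 0.046 is still large beside a small QALY gain. This also stands.

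Fourth, the gain depends on a correlation across knee replacement surgery that the documents do not give, and it vanishes if that correlation is near zero. This is why the range has to be shown.

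**Conclusion.** The point holds as a worthwhile improvement to a stated comparison. It does not make the analysis invalid. Its size is the 18 to 42% cut in variance at ρ of 0.3 to 0.5, or about 16 to 40% after paying for the slope. It rests on the trapezoid rule, equal SDs and the assumed correlations.

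A reader might infer that chance imbalance can exceed the whole training effect. The documents do not support this, because they give no EQ-5D SD, no correlation and no expected utility or QALY gain. Taking hypothetical effects over SD 0.15 to 0.30, the probability that the baseline-explained shift exceeds the effect is:

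| Hypothetical effect | ρ = 0 | ρ = 0.3 | ρ = 0.5 |
|---|---|---|---|
| 0.02 QALY | 0–12% | 28–63% | 47–74% |
| 0.05 QALY | about 0% | 1–23% | 7–41% |
| 0.10 QALY | 0% | 0–2% | 0–10% |

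The effect itself is just as uncertain. With weights (6, 29, 23)/52, a 6-week gain of 0.025 to 0.05 utility is worth 29/52 of that, 0.014 to 0.028 QALY, if it has gone by 12 months. If it is fully kept, it is worth (29 + 23)/52 of that, 0.025 to 0.05. The comparison therefore sets one assumption against another.

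**What to change.** In Economic evaluation, state that incremental QALYs are estimated by regression on arm with baseline EQ-5D utility as a prespecified covariate, whatever the baseline test shows. Bootstrap this jointly with costs. Use the adjusted difference for the cost-effectiveness conclusion and the acceptability curve. The unadjusted arm means can be reported alongside.

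The cost is one model term. Baseline EQ-5D is already scheduled, so no visit, questionnaire or sample-size change is needed. The only statistical price is the loss of about 1 to 2% of variance if baseline turns out to be unrelated to follow-up. Fixing the covariate before the arms are compared also removes a later choice that could affect the economic conclusion.
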